**Erasmus MC**		
**Ikazia Ziekenhuis**	4.5	10
**Franciscus Gasthuis & Vlietland, location Gasthuis**	5.4	14
**Franciscus Gasthuis & Vlietland, location Vlietland**	7.5	14
**Maasstad Ziekenhuis**	8.9	20
**IJsselland Ziekenhuis**	10.4	22
**Van Weel Bethesda Ziekenhuis**	55.0	49
**Albert Schweitzer Ziekenhuis**		
**Beatrixziekenhuis**	25.4	23

^a^Estimated with ArcGIS Online Software version 10.6.1.

**Table 2 TB2:** Description of the control region.

Hospital	Distance from intervention centre (km)	Estimated driving time (min) ^a^
**Amsterdam UMC, location AMC**		
**Amsterdam UMC, location VUmc** ^**b**^	10.0	10
**OLVG West**	15.3	14
**Spaarne Gasthuis**	27.9	21
**Flevoziekenhuis**	29.3	24
**Rode Kruis Ziekenhuis**	35.9	26
**Dijklander Ziekenhuis, location Purmerend**	38.3	28
**Dijklander Ziekenhuis, location Hoorn**	56.8	37
**Noordwest Ziekenhuisgroep, location Alkmaar**		
**Noordwest Ziekenhuisgroep, location Den Helder**	43.1	43

^a^Estimated with ArcGIS Online Software version 10.6.1.

^b^Closed for acute stroke care in the spring of 2023.

For the secondary objective, we will include all consecutive adult patients (≥18 years) with a suspected stroke (based on a positive FAST-test [≥1 point, except for isolated dysarthria]) with onset of symptoms within the last 24 h for whom the Stroke Triage App was utilised in the intervention region during the study period.

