### Objectives

The primary objective of the PRESTO-2 study is to evaluate whether regional implementation of prehospital triage with the Stroke Triage App, compared with standard prehospital care without triage optimisation (ie, a drip-and-ship strategy), is associated with changes in onset-to-groin time in patients with ischaemic stroke due to LVO undergoing EVT, and with changes in onset-to-needle time in patients with ischaemic stroke without LVO. The secondary objective is to evaluate the implementation of the Stroke Triage App in the intervention region, in terms of logistics (over- and undertriage proportions and patient distribution), patient outcomes (proportion of patients treated with IVT and EVT) and user metrics (app usage, number of users and compliance among paramedics).

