#### Secondary objective

For the secondary objective, outcome measures will be the distribution of final diagnoses (ischaemic stroke with LVO, ischaemic stroke without LVO, TIA, intracerebral haemorrhage and stroke mimics) in PSC and intervention centres, the number and percentage of ischaemic stroke patients without EVT-eligible occlusion taken to an intervention centre after bypassing a PSC (overtriage), the number and percentage of ischaemic stroke patients with an EVT-eligible occlusion who were not bypassed to an intervention centre (undertriage), the number of triages per month, number of users per month, number of uses per paramedic per month, compliance, adherence to the Stroke Triage App advice, total number of required acute ambulance transportations (prior to reperfusion therapy) and total number of required subacute ambulance transportations (transfers after reperfusion therapy or in absence of an indication thereof).

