### Data analysis plan

The statistical analysis will be performed after inclusion of the last patient, after the data have been checked, errors have been corrected and the database has been locked. Missing data will be handled via simple imputation (if < 5% missing) or multiple imputation by means of a multiple regression model (if ≥ 5% missing). We will estimate the effect of the implementation of the Stroke Triage App on the primary and secondary outcomes of the primary objective using difference-in-differences linear regression analysis. This analysis compares the differences before and after implementation in the implementation region with the differences between the same periods in the control region where no implementation takes place. This method adjusts for unobserved confounders and (other) time-related differences in acute stroke care. For the secondary objective, we will report the observed outcomes in the study cohort. We will then conduct counterfactual simulation assuming transport to the nearest hospital, in accordance with the ambulance protocol that was in place prior to the implementation of the Stroke Triage App (“drip-and-ship” model). We will compare the observed outcomes with the simulated outcomes in order to be able to make a statement about the effects of the implementation of the Stroke Triage App on these outcomes. Closure of the database and analysis of the data is planned after submission of the protocol for publication. A detailed Statistical Analysis Plan can be found in the Supplementary Materials.

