### Duration and current status of the study

The study started on 22nd January 2024, when the Stroke Triage App went live and was incorporated into the regional protocols for ambulance care. Due to lower-than-expected compliance and usage of the Stroke Triage App, the study protocol was amended to facilitate an interim analysis allowing for re-estimation of the sample size. During this interim analysis at 9 months after implementation, the usage rate of the Stroke Triage App was evaluated. It was determined that the Stroke Triage App was used for triage in 33% of patients eligible for EVT. Based on the revised effect size of the intervention, a new sample size calculation was conducted. Assuming a reduced effect size of 33%, we estimated that the Stroke Triage App would need to be used for triage of 274 patients eligible for EVT in the national DASA registry. Therefore, the study group decided that the study duration could be prolonged by a maximum of 12 months. Initially, enrolment was planned to finish on 22nd January 2025. This deadline was extended to 31st December 2025 to meet the requirement of the new sample size calculation.

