Within this context, this study has several notable strengths. The Stroke Triage App contains a decision model incorporating the most important aforementioned variables to calculate the probability of a good functional outcome for 2 transportation strategies for each individual patient. This personalised approach to prehospital triage allows for the Stroke Triage App to more easily be implemented in other regions with different regional characteristics. Prior to implementation of the Stroke Triage App, the effectiveness of the triage algorithm was established through modelling in a real-world cohort of suspected stroke patients in the region, supporting implementation of the application as a CE-compliant medical device.^21^ To evaluate the effectiveness of implementation of the Stroke Triage App, we considered utilising a randomised controlled trial design, but this approach would come with significant drawbacks. First, patient inclusion and randomisation to different transportation strategies would be a time-consuming process, adversely affecting the study population with treatment delays. Second, individual patient randomisation would likely have resulted in contamination of the control arm. After training in the use of the Stroke Triage App, paramedics may consciously or subconsciously incorporate the app’s triage logic into decision-making for patients allocated to standard care. This would diminish the contrast between intervention and control conditions and compromise the ability of the study to estimate the true effect of implementation. Third, the study aimed to evaluate the effectiveness of actual implementation of prehospital triage with the Stroke Triage App, including factors such as suboptimal paramedic compliance and non-adherence to the advice due to unforeseen circumstances. Finally, obtaining informed consent prior to or deferred consent after inclusion posed substantial logistical challenges, as previously described in the Methods section. Given that the Stroke Triage App was implemented as part of routine clinical care, we chose to utilise a pragmatic, non-randomised controlled before-and-after intervention design instead. This quasi-experimental design enables comparison with a control group, while the difference-in-differences analysis also adjusts for temporal trends in the improvement of treatment times for acute ischaemic stroke. One challenge in the study design was identifying a comparable control region without prehospital triage. Although distances between PSCs and intervention centres differed slightly between regions, these differences were stable over time and are therefore unlikely to bias the estimated intervention effect. As such, we expect the between-region differences before and after implementation to primarily reflect underlying temporal trends. Another challenge of this study was selecting an appropriate outcome measure. Onset-to-groin time in patients undergoing EVT reflects the potential benefits of the intervention, whereas onset-to-needle time in patients receiving IVT reflects its potential adverse consequences. A composite outcome was considered, but this was not feasible due to the expected high proportion of missing 3-month mRS scores in the DASA registry. Moreover, combining these time-based outcomes was methodologically challenging, as minutes gained in onset-to-groin time are not directly comparable to minutes lost in onset-to-needle time. To account for patients who may have forgone treatment as a result of triage decisions, we additionally report the proportion of patients receiving EVT and IVT.

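### The secondary-objective triage and transport results come from app users only, so they cannot be stated as effects of implementation in the region

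*Protocol article*

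**What the plan says.** All references are to the protocol article.

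- **Who is in the cohort.** Study population (paragraph after Table 2) includes, for the secondary objective, suspected stroke patients "for whom the Stroke Triage App was utilised in the intervention region during the study period". Data collection starts from what is entered in the app and uses the ride number to reach the ambulance-service records.
- **What the cohort is for.** Objectives states: "The secondary objective is to evaluate the implementation of the Stroke Triage App in the intervention region, in terms of logistics". It goes on to patient outcomes and to "user metrics (app usage, number of users and compliance among paramedics".
- **What is measured.** Outcome measures, Secondary objective, lists diagnosis distribution by type of centre, over- and undertriage (numbers and percentages), and acute and subacute ambulance transports. It also lists "number of uses per paramedic per month, compliance, adherence to the Stroke Triage App advice".
- **What will be concluded.** Data analysis plan compares observed outcomes with simulated nearest-hospital transport in order to "make a statement about the effects of the implementation of the Stroke Triage App on these outcomes".
- **How much the app was used.** Duration and current status reports that, at nine months, "the Stroke Triage App was used for triage in 33% of patients eligible for EVT".

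**The concern.** A FAST-positive patient for whom the paramedic did not open the app has no stated route into this dataset. The triage and transport outcomes are therefore results among patients triaged with the app. The objective and the planned conclusion are worded for the implementation in the region, which includes rides where the app stayed closed.

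At the reported usage this matters. A reader shown an undertriage percentage, and its reduction against simulated drip-and-ship, would take it as what happened to EVT-eligible patients in the region, although the cohort may hold only about a third of them. Users may also differ from non-users, for example if paramedics choose when to open the app. The article gives no data on this, so the direction of any such selection is unknown.

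The sample-size re-estimation for the primary outcome lowered the assumed effect because of low usage. The article states no corresponding qualification for the secondary objective.

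**Working it through.** **The plan's own figure.** The 33% in Duration and current status is given without numerator or denominator, so it cannot be rebuilt. It is taken as stated; its complement is 67%. It applies to EVT-eligible patients at nine months. The article gives no usage rate for all FAST-positive rides or for patients without an EVT-eligible occlusion.

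**Step 1: which outcomes the cohort can support.**
- Supported as planned: triages per month, users per month, uses per paramedic, adherence to the advice.
- Supported for app users only: over- and undertriage percentages, diagnosis distribution, transport counts, and the observed-versus-simulated comparison.
- Not obtainable from the cohort alone: compliance, if it means using the app for an eligible patient. Inside the cohort that is users divided by users, or 100%.

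**Step 2: how the effect in users relates to the regional effect.** Let u be usage, a and b the undertriage rates in users and non-users, and s_u and s_n the simulated nearest-centre rates in the two groups.

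- Effect in the cohort: s_u − a
- Effect in the region: u(s_u − a) + (1 − u)(s_n − b)

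If non-users went to the nearest centre, then b = s_n and the second term is zero. The regional percentage-point effect is then u times the cohort effect, whatever the value of a.

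**Step 3: numerical illustration.** Take EVT-eligible patients whose nearest centre is a primary stroke centre. Nearest-centre transport then gives 100% undertriage by definition. Assume a = 40% and b = 100%; neither is in the article.

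- Cohort: undertriage 40%, reduction 100 − 40 = 60 points.
- Region: 0.33 × 40 + 0.67 × 100 = 80.2%, reduction 19.8 points = 0.33 × 60.
- Ratio of the two reductions: 60 / 19.8 = 3.03 = 1 / 0.33.

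Now count patients. As a simplification, treat the roughly 400 annual EVTs (Sample size calculation) as all falling in this group: 0.33 × 400 = 132 inside the cohort and 268 outside.

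- Cohort: 132 × 0.60 = 79.2 fewer undertriaged patients.
- Region: 400 × 0.198 = 79.2.

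Under this assumption the absolute change is the same; only the percentages depend on the denominator. The same holds for the change in transport counts, because non-users then contribute no observed-minus-simulated difference.

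**Step 4: without the nearest-centre assumption.** Regional undertriage = 0.33a + 0.67b:

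| Users (a, assumed) | b = 0% | b = 50% | b = 100% |
|---|---|---|---|
| 20% | 6.6% | 40.1% | 73.6% |
| 30% | 9.9% | 43.4% | 76.9% |
| 40% | 13.2% | 46.7% | 80.2% |

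With users at 30%, the region could lie anywhere from about 10% to 77% if nothing is known about non-users, and from 43% to 77% if their rate is 50% to 100%. The cohort cannot narrow this.

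**Step 5: does the primary analysis fill the gap?** It takes registry patients in both regions whether or not the app was used, so non-use is included. Its outcomes are onset-to-groin and onset-to-needle times, proportions treated within the time windows, and mRS. None is a triage or transport outcome, and the registry variables listed in Data collection include no bypass or route field.

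**The case against.** **Compliance is measurable in the study.** This stands. The 33% shows that a denominator outside the app cohort has already been obtained. The article does not define compliance, Objectives lists it apart from app usage, and the statistical analysis plan, which is not shown, may define it. A reader might infer that the trial can only report 100% compliance; the article does not support that. What remains is that the stated cohort cannot supply the denominator. Defining compliance would also not change the population behind the triage and transport percentages.

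**Non-use is evaluated elsewhere.** This stands too. The Discussion's aim of evaluating actual implementation, "including factors such as suboptimal paramedic compliance and non-adherence to the advice due to unforeseen circumstances", explains the choice of design for the study as a whole. The primary registry analysis meets it for treatment times, treatment proportions and mRS. It would be wrong to say that the trial removes non-use from its evaluation. As Step 5 shows, this does not extend to triage and transport outcomes.

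**A three-fold overstatement is not established.** This stands as well. The ratio needs every non-user to have gone to the nearest centre. The Discussion itself notes that trained paramedics may apply the app's logic to other patients, which makes that doubtful. The ratio concerns percentages only, while the article reports over- and undertriage as numbers as well, and transports as totals. Nor does the 33% show that all remaining EVT-eligible patients came by ambulance or met the app's criteria.

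**The cohort rule is disclosed, and an on-use cohort is legitimate.** Both are true. The fault is not in studying app users, but in the wording of the objective and conclusion drawn from them.

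**Conclusion.** The point holds as a mismatch between population and conclusion in the secondary objective. Over- and undertriage percentages, diagnosis distribution, transport counts and the observed-versus-simulated comparison describe patients triaged with the app. The article presents them as an evaluation of implementation in the region.

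At 33% usage, and only if non-users went to the nearest centre, the regional percentage-point effect on undertriage among EVT-eligible patients would be about one third of the effect in users, with the same absolute number of patients affected. Without that assumption the regional percentage is not identified from this cohort. The 33% is an interim rate, final usage may differ, and it cannot be carried over to overtriage.

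The primary objective is unaffected. The documents do not support the stronger readings that compliance cannot be measured in the trial, or that the reported benefit is known to be inflated three-fold.

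**What to change.** 1. In Objectives, Outcome measures (Secondary objective) and Data analysis plan, state that the triage, distribution and transport results, and the observed-versus-simulated comparison, apply to patients triaged with the app. Word the planned conclusion as an effect among those patients.
2. Compute compliance, in the sense of app use, on a denominator from outside the cohort: the source of the 33% figure, or aggregate ambulance-service counts of eligible rides if they can be supplied. Report that usage rate beside the triage results.
3. If a regional undertriage figure is wanted, give it only as a sensitivity calculation. State the assumption about non-users and show a range, as in Step 4. A full regional estimate is not shown to be feasible, because the listed registry variables have no bypass or route field and scaling by usage imposes an untested assumption.

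The article plans database closure and analysis after submission of the protocol, so the change is best dated before the secondary results are examined. The cost is some rewording and a little extra analysis. The availability of the ambulance counts has to be confirmed. Headline figures will look less favourable when read beside the usage rate.

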### Data collection

Two separate datasets will be collected for the analysis of the 2 objectives. For the primary objective, data will be collected from the national stroke care quality registry (the Dutch Acute Stroke Audit [DASA] of the Dutch Institute of Clinical Auditing [DICA]). All Dutch hospitals report data regarding patient characteristics, process and outcome indicators to this registry annually. These registry data are used to prevent bias and disparities in the before-and-after intervention population cohorts in the intervention region and to control for time-dependent improvement in treatment times. To minimise the risk of double inclusions, patients receiving IVT will be included only if they were not transferred between hospitals. Patients undergoing EVT will be included solely from intervention centres. We will collect data including clinical characteristics (age, sex, type of stroke onset, date and time of stroke onset, NIHSS score and diagnosis), workflow and treatment indicators (date and time of presentation at Emergency Department, given treatment, door-to-needle time in case of IVT, door-to-groin time in case of EVT) and outcome indicators (mRS score after 3 months).

For the secondary objective, we will collect data gathered in the ambulance that is entered into the Stroke Triage App, consisting of the ambulance ride number, GPS location, time of symptom onset or last known well and individual RACE scale items. We will also collect data which are automatically generated by the Stroke Triage App, consisting of the onset-to-departure time, probability of LVO based on the RACE scale sum score and driving times to various hospitals, as well as workflow metrics consisting of login time and total duration of triage. The ambulance ride number is used to identify patients from the EMS databases, in order to collect data regarding demographics, vital functions, general examination, transportation times and complications (ie, vomiting, aspiration and neurological deterioration) occurring during transportation. After transportation to the hospital, suspected stroke patients will undergo standard diagnostic work-up at the discretion of the attending physician. This work-up may consist of laboratory testing, non-contrast enhanced CT scan, CTA, CTP and/or digital subtraction angiography. No additional testing is performed within the context of this study. We will collect data regarding medical history, physical and neurological examination, diagnostic tests, diagnosis and administered treatment, including specific workflow times when applicable, from the hospital electronic health records.

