## Introduction

The effectiveness of both available acute reperfusion therapies for ischaemic stroke, intravenous thrombolysis (IVT) and endovascular thrombectomy (EVT), decreases as time elapses.^1–5^ IVT is available in most primary stroke centres (PSCs) and has a relatively broad indication, while EVT is only available in specialised intervention centres and is restricted to patients with LVO.^6–9^ Approximately one-quarter of patients with acute ischaemic stroke have a proximal intracranial LVO.^10^ The effect of IVT in this group of patients is small, but EVT is highly efficacious.^7^^,^^8^^,^^10^^,^^11^

Interhospital transfers are required for patients with an LVO stroke when they have first been transported to the nearest PSC, causing delay to initiation of EVT.^12^^,^^13^ Prehospital triage aims to eliminate these interhospital transfers by identifying these patients in the ambulance, allowing immediate transportation to an intervention centre. Various tools for detecting or estimating the likelihood of LVO have been developed to facilitate prehospital triage. Among these tools, prehospital stroke scales are the most widely used and investigated.^10^^,^^14^ When the total score of the prehospital stroke scale for a patient is above a defined cut-point, the patient is directly transported to the intervention centre.^15^^,^^16^ Prehospital stroke scales are implemented in several ambulance regions in the Netherlands and beyond to facilitate prehospital triage decision making, although a benefit of implementation of these scales on long-term functional outcome has not been unequivocally established.^17^ These scales do not account for essential regional characteristics, such as driving times to hospitals, workflow times within hospitals and transfer times between hospitals, while previous research showed that these are also important factors in determining the optimal transportation strategy besides stroke severity.^13^ These factors are combined with one of the best performing prehospital LVO detection scales, the Rapid Arterial oCclusion Evaluation (RACE) scale, into a decision support tool, the Stroke Triage App.^10^^,^^13^^,^^14^^,^^18^ The Stroke Triage App consists of an algorithm combining these factors in a multivariable decision model to aid ambulance staff in determining the best transport strategy for each individual patient.^19^^,^^20^

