### Outcome measures

#### Primary objective

The primary outcome measure for the primary objective will be the symptom onset or last known well time to groin puncture time (start of EVT) in patients with an ischaemic stroke with LVO who presented in the emergency department within 6 h from stroke onset. Secondary outcome measures for the primary objective will be the symptom onset to needle time (start of IVT) in patients who are treated with IVT, the percentage of patients with ischaemic stroke treated with IVT within the conventional guideline-recommended time window of 4.5 h after symptom onset or last seen well, the percentage of patients with ischaemic stroke treated with EVT within the conventional guideline-recommended time window of 6 h after symptom-onset or last seen well and the mRS score after 3 months.

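### Excluding transferred IVT patients selects on the event the app is meant to prevent, which can raise the IVT percentage artificially and mask forgone treatment

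*Protocol article*

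**What the plan says.** The Data collection section sets two selection rules for the registry dataset. For thrombolysis: "To minimise the risk of double inclusions, patients receiving IVT will be included only if they were not transferred between hospitals". For thrombectomy: "Patients undergoing EVT will be included solely from intervention centres". The stated reason is to avoid counting a patient at both hospitals.

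The Introduction gives the purpose of the intervention: "Prehospital triage aims to eliminate these interhospital transfers by identifying these patients in the ambulance, allowing immediate transportation to an intervention centre".

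The onset-to-needle population is described in two ways. The Objectives refer to "changes in onset-to-needle time in patients with ischaemic stroke without LVO". Under Outcome measures, Primary objective, the outcome is "the symptom onset to needle time (start of IVT) in patients who are treated with IVT", with no restriction on LVO. The percentage treated with IVT within 4.5 h is defined among patients with ischaemic stroke. The article does not say whether transferred IVT patients remain in that denominator.

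The Discussion presents onset-to-needle time as the measure of possible adverse consequences, and the proportions receiving IVT and EVT as the check on patients who may have forgone treatment because of triage.

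**The concern.** Transfer happens after the triage decision and is the event triage is designed to change, so selecting on it means selecting on a consequence of the intervention. Before go-live, an LVO patient who receives IVT at a primary stroke centre and is sent on for EVT fails the IVT rule. After go-live, the same patient taken straight to an intervention centre passes it. The IVT cohort therefore gains LVO patients without anyone's treatment having changed.

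The Study population section says the control region had no individualised triage, so its before-after change does not contain this app-driven shift. Difference-in-differences subtracts trends common to both regions; it cannot subtract selection confined to one region and one period.

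At stake are the outcomes meant to show harm. Under the literal rule the artefact in the IVT percentage is upward or, on one reading of the denominator, possibly nil. An upward artefact works against detecting a real loss of IVT.

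**Working it through.** The article gives no expected value for IVT percentage or onset-to-needle time, so there is no figure of its own to reproduce. The check asks what the rule does when no patient's treatment or needle time changes.

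**Inputs**
- LVO share 25% (Introduction, about one-quarter).
- App used in 33% of EVT-eligible patients at the interim look (Duration and current status of the study).
- Assumptions not in the article: share p of LVO patients first at a primary stroke centre and transferred, 55% (range 40–70%); IVT in 50% of LVO and 25% of non-LVO patients; full app use would cut transfers by 60%, so one-third use cuts them by 20%.

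Hence p = 0.55 before go-live, 0.55 × 0.80 = 0.44 at one-third use, and 0.55 × 0.40 = 0.22 at full use.

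**IVT percentage**

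Counted IVT = 0.75 × 0.25 + 0.25 × (1 − p) × 0.50 = 0.1875 + 0.125 × (1 − p). The true share is 0.1875 + 0.125 = 31.25% in both periods.

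Three denominators are possible:
- A: all patients (1).
- B: transferred IVT patients removed (1 − 0.125p).
- C: all transferred LVO patients removed (1 − 0.25p).

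| p | A | B | C | LVO share of IVT cohort |
|---|---|---|---|---|
| 0.55 | 0.2438 | 0.2438/0.9313 = 0.2617 | 0.2438/0.8625 = 0.2826 | 0.0563/0.2438 = 23% |
| 0.44 | 0.2575 | 0.2575/0.9450 = 0.2725 | 0.2575/0.8900 = 0.2893 | 0.0700/0.2575 = 27% |
| 0.22 | 0.2850 | 0.2850/0.9725 = 0.2931 | 0.2850/0.9450 = 0.3016 | 0.0975/0.2850 = 34% |

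Change with no true effect, in percentage points:
- One-third use: A +1.4, B +1.1, C +0.7.
- Transfers cut by 60%: A +4.1, B +3.1, C +1.9.

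Over p = 0.40 to 0.70 at one-third use, the shift under A is 0.125 × 0.20 × p, or 1.0 to 1.75 points. Under C it runs from 0.2725/0.9200 − 0.2625/0.9000 = 0.5 points to 0.2425/0.8600 − 0.2250/0.8250 = 0.9 points.

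A second set of assumptions varies the IVT rates: 50–70% of LVO patients transferred, IVT in 40% of non-LVO and 40–60% of LVO patients, and 10–33% of the transferred patients redirected. It gives +0.5 to +3.5 points under A, +0.3 to +2.3 under B, and 0 to +1.2 under C. Under C the shift is exactly 0 when LVO and non-LVO patients have the same IVT rate.

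**Onset-to-needle time, all IVT patients**

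Shift = (change in LVO share) × (LVO minus non-LVO mean onset-to-needle time). At one-third use the share rises by 4.1 points (23.1% to 27.2%). An assumed gap of 10 to 30 min gives 0.041 × 10 = 0.4 to 0.041 × 30 = 1.2 min. The second set of assumptions gives 0.1 to 2.4 min. The sign is that of the gap, which the article does not give.

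**Transfers after treatment**

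The secondary-objective outcomes foresee ambulance transfers after reperfusion therapy. If these count as transfers under the IVT rule, bypassed non-LVO patients who receive IVT and are then moved on drop out, and they are the ones who carry the delay. With share b bypassed, delay d and share e moved on, the true mean delay is b × d and the measured delay is b(1 − e)d/(1 − be). For assumed b = 0.10, d = 20 min and e = 0.5, the true value is 2.0 min and the measured value is 1.0/0.95 = 1.05 min. With e = 1 the measured value is 0.

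**Under the alternative count**

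Counting every IVT once at the hospital that gave it leaves the IVT percentage at 31.25% and the LVO share of the IVT cohort at 0.125/0.3125 = 40% in both periods. The artefact is zero.

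**The case against.** The case against is mainly about size and certainty, and much of it stands.

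- **Size.** A reader might take +4.1 points, or a move to a 34% LVO share, as the expected artefact. The article does not support that. Both need a 60% fall in transfers, whereas reported app use was 33%, and +4.1 also keeps excluded patients in the denominator as if untreated. If the rule removes them from the dataset, B or C applies.
- **Onset-to-needle time.** A reader might infer that this outcome is bound to be biased. If the non-LVO population in the Objectives governs, the LVO channel largely closes, and only the post-treatment transfer channel remains, which depends on what counts as a transfer. The analysis plan, not shown, may settle the population. The article's two descriptions still differ.
- **Double counting.** One might also infer that untreated transferred patients are counted at both hospitals, so that denominators shrink as transfers fall. The article does not say how untreated patients are de-duplicated and may leave this to the full plan, so that is speculation.
- **Primary outcome.** The IVT rule does not touch onset-to-groin time, because EVT patients are selected separately.
- **Feasibility.** The Ethical aspects section describes the registry data as not personally identifiable, and the article does not establish that records can be linked across hospitals. A remedy that needs linkage cannot be assumed cheap. Restricting onset-to-needle time to patients given IVT without EVT would also condition on something triage may change.

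None of this removes the mechanism for the IVT percentage, which follows from the stated rule and the stated purpose of triage.

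**Conclusion.** The concern holds for the IVT outcomes. The inclusion rule depends on a post-intervention event that the app changes in one region and one period, and difference-in-differences does not correct for that. On the assumed inputs, the IVT percentage rises by about 0.7 to 1.4 points at one-third usage with no real change in treatment; the span reflects the unstated denominator. It would be 1.9 to 4.1 points only if transfers fell by 60%. Onset-to-needle time could move by up to a few minutes in an unknown direction if all IVT patients are analysed. Its measured delay would be understated if transfers after treatment trigger exclusion. These sizes rest on transfer shares, IVT rates and time gaps that the article does not give. Because only secondary outcomes are affected, this is something that should be fixed, not a threat to the primary analysis.

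**What to change.** For the IVT outcomes only, leaving EVT selection unchanged:

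1. Count each IVT once, at the hospital that gave it. Keep the primary stroke centre's record when the patient is later transferred, and drop the transferred-in record at the receiving centre.
2. Count each patient once in the denominator, at the first hospital, and state this.
3. Define transfer explicitly, separating transfers before and after treatment.
4. Reconcile the onset-to-needle population between the Objectives and the Outcome measures, without defining it by receipt of EVT.
5. Keep the current non-transferred rule as a sensitivity analysis, and report the transferred share by region and period.

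The cost is selection code and analysis plan wording. The count relies on the transfer field that the present rule already needs, though it should be confirmed that the field identifies transferred-in records at the receiving centre. The downside is a few residual duplicates where that field is miscoded. The Data analysis plan section places database closure and analysis after submission of the protocol. If the analysis has already been run, the revised count should be reported beside the planned one and labelled as a change.
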